#### Non-adapted brief motivational intervention (NA-BMI)

Consistent with MI, the core NA-BMI components include: 1) personalized feedback based on screening and baseline assessment, 2) exploring decisional balance of alcohol use from patient’s perspective, 3) building motivation for change through the assessment, and discussion of patients’ self-report of levels of importance, confidence, and readiness to change, 4) enhancing commitment to change by exploring patient’s options for change, and developing a change plan if indicated, and 5) providing alcohol treatment referrals. The NA-BMI will not target cultural risk or protective factors beyond any normal tailoring that may occur in standard BMI. Personalized feedback will be based on U.S. general population drinking norms, and frequency of alcohol problems.

#### Culturally adapted brief motivational intervention (CA-BMI)

CA-BMI also adheres to the core principles of both MI and BMI. In CA-BMI, core components of BMI are adapted to be responsive to the unique risk (i.e., acculturative stress) and protective (i.e., familism) factors associated with heavy drinking, alcohol problems, help-seeking, and treatment utilization in Hispanics. CA-BMI goes beyond any tailoring that may occur in NA-BMI by targeting important predictive factors of drinking in Hispanics. Two *primary* adaptations to CA-BMI will be made.

First, CA-BMI will incorporate the assessment, and personalized feedback on the impact of acculturative stress on drinking in order to decrease temptation to drink, and increase confidence to avoid drinking. Participants will receive feedback about the types, and intensity of acculturative stress they may experience (e.g., immigration-related issues, cultural congruity), and clinicians will evoke the relation of acculturative stress to temptation, and confidence to avoid drinking. Second, CA-BMI will integrate family, and community as reasons for change, and as agents of behavior change when considering the impact of drinking, plans for changing drinking, and engagement in help-seeking behaviors. Similar to methods developed by Lee et al. (2011) [63] and Añez et al. (2008) [64], the CA-BMI will incorporate a discussion of how social context and family dynamics may affect drinking. Feedback, and a discussion of social pressures (e.g., cultural gatherings) to engage in heavy drinking as well as changes in drinking patterns (e.g., concerns about drinking from family) will also be included. When developing a change plan, there will be an explicit discussion, and elaboration of changes in family or community networks that may facilitate reductions in drinking. Participants will be encouraged to identify, and actively engage family and community members as helpers in their efforts to change their drinking. For example, they may identify a respected member of the family or community with whom they can talk about their commitment to change. Participants’ cultural norms, expectations, and personal values will be discussed to illuminate discrepancies with current drinking behavior, which may increase motivation to change (see Añez et al., 2008 [64]).

These two central modifications result in a culturally adapted intervention that is substantially distinct in content, and focus from a non-adapted intervention, while still maintaining consistency with MI, and its application within brief alcohol interventions. Based on adaptations, we anticipate the potential mediators or mechanisms of behavior change specific to CA-BMI to be: 1) temptation to drink and confidence to avoid drinking, and 2) increased support from family, and friends in general as well as specific support to change drinking, and seek treatment. We will evaluate a definition of treatment utilization that is more comprehensive than that in our prior study, which assessed the use of formal inpatient/outpatient substance abuse treatment, and attendance to self-help groups such as Alcoholics Anonymous [20]. We will assess engagement in formal treatment networks as well as informal help-seeking common among Hispanics (e.g., family, religious leaders).

### Training and treatment fidelity

#### Interventionists

We have determined that Hispanics respond more positively to BMI, and that patient—provider ethnic matching significantly influences drinking outcome above and beyond the effect of the intervention. Both NA-BMI and CA-BMI will be provided by bilingual, bicultural, and same gender interventionists. Therefore, gender, ethnicity, and ability to speak both Spanish, and English will be held constant across interventions. By holding these three factors constant we can determine the differential influence of the two interventions on alcohol-related outcomes. To avoid contamination, providers of CA-BMI and NA BMI will be trained, and supervised separately throughout the study period. Study staff who are responsible for the intervention will not be responsible for baseline or follow-up assessments.

#### Interventionist training and supervision

[name], the Principal Investigator (PI), will be primarily responsible for oversight of the training, and supervision of interventionists. [name] has received advanced training in MI (including the use of treatment fidelity measures for supervision), and is a member of the Motivational Interviewing Network of Trainers (MINT). [name], a Co-investigator (Co-I), will facilitate training, and supervision. [name] is a bilingual, bicultural clinical psychologist with expertise in culturally sensitive service provision, and extensive experience in providing Spanish-language services to Hispanic populations. [name] has experience with cultural adaptations of smoking cessation interventions based on MI [49]. Training manuals for CA-BMI will be adapted from existing brief intervention manuals from previous trials (R01-AA13824; R01-AA015439) conducted by the PI. As part of the training process, the PI’s research team has developed a set of training videos that will serve for the purposes of both NA-BMI and CA-BMI training. These short videos portray typical BMI sessions through role plays including study investigators providing BMI. Prior to training, interventionists will read *Motivational Interviewing* [16], read the intervention manual (CA-BMI or NA-BMI), and watch the aforementioned videos. A two-day interactive training on MI principles, and the practice of brief interventions will be provided by a bilingual trainer who is a member of the MINT. In addition to the study PI and Co-I, a Training Coordinator, [name] will be primarily responsible for the training and supervision of interventionists. [name] has received advanced MI training, and is also a member of the MINT. Supervision will be provided by [name] throughout the study, and will include the following: 1) weekly supervision, 2) on-site observation, feedback, and/or coaching sessions (at least one per month), and 3) a one-day booster training provided every six months. This provides trainees the opportunity to practice, receive feedback, and refine their skills.

#### Treatment fidelity

Procedures to ensure treatment fidelity are based on recommendations from the NIH Behavior Change Consortium [65], which established best practices in treatment fidelity of behavioral interventions. Fidelity will consist of two components: 1) *adherence*, or whether the interventionist carried out specified procedures of CA-BMI or NA-BMI, and 2) *competence*, or the interventionist’s level of skill in implementing the intervention using MI. Adherence to CA-BMI or NA-BMI protocols, and competence in MI will be assessed throughout the study by reviewing and coding recorded interventions.

#### Adherence to CA-BMI and NA-BMI

Intervention protocols will be codified using behavioral checklists, which have been found to be useful in monitoring intervention delivery [66]. These will be based on checklists from our prior studies (R01- AA13824; R01-AA015439 and R01-DA026088). The CA-BMI checklist will be adapted from a current checklist used to assess BMI adherence [19]. Interventions will be coded using a checklist based on prescribed, and proscribed components of the respective BMI. Adherence checklists will be used in supervision, and to establish adherence and discriminability between CA-BMI, and NA-BMI.

#### Competence in MI

Interventionists’ competence will be assessed in both BMIs using the Motivational Interviewing Treatment Integrity (MITI) v3.1 [67]. The MITI is a behavioral coding system that measures competence in MI by assessing the degree to which therapist behaviors are adherent or non-adherent to MI. Supervisors will complete the MITI on audio recordings of BMIs throughout the recruitment period. The MITI will be used to derive summary scores with benchmarks for basic, and expert proficiency in MI. We will use expert-level performance as the threshold for establishing, and maintaining competency. MITI summary scores will be used to provide feedback during supervision, and to demonstrate competence in MI.

#### Assessment of patient-oriented outcomes

This study will employ bilingual staff to conduct the assessments, which facilitates the option of reading questions aloud to participants, thereby assisting patients to complete the in-person baseline assessment during their hospital stay [68]. All measures used were developed or tested in Spanish, and are available in both Spanish, and English. Staff responsible for baseline and follow up assessments are blind to participants’ intervention condition, and will be trained and supervised throughout the recruitment period.

### Measures

#### Drinking outcomes

*The Timeline Follow Back (TLFB)* will be used to obtain data on the prior month’s days of alcohol use, calculated average weekly drinks, days of binge use, average number of drinks per drinking day, maximum number of drinks on any day, and drinking above at-risk levels [69, 70]. *The Short Inventory of Problems (SIP + 6)* will be used to assess the number of alcohol-related consequences as an outcome variable. The SIP + 6 is a brief version of the Drinking Inventory of Consequences (DrInC) [71]. The SIP + 6 contains five 3-item scales related to consequences in the physical, social responsibility, intrapersonal, impulse control, and interpersonal domains. This scale has been validated with both English and Spanish speaking Hispanics [72].

#### Treatment utilization

*The Treatment Services Review (TSR)* will be used to collect information regarding the receipt of services for seven potential problem areas—medical status, employment and support, drug use, alcohol use, legal status, family/social status, and psychiatric status [73, 74]. To complement this measure, the *Mexican American Prevalence and Services Survey (MAPS)* will be used to assess help seeking [51] through other methods, such as chiropractor, homeopath, minister, folk healer (i.e., curandero), spiritualist, santero, and sobador.

#### Social support

Social support will be measured using four subscales including social cohesion, support from friends and family, and family cultural conflict [75]. The *Important People and Activities (IPA)* interview will complement the assessment of general social support by assessing social support specific to alcohol use [76, 77]. The IPA assesses support from family and friends through both structural, and functional processes. The IPA also assesses how people within the patient’s social network would react to the patient’s drinking on a five point Likert type scale ranging from 1 (*left or made you leave*) to 5 (*encouraged your drinking*).

#### Temptation and confidence

Situational temptation to drink will be measured using the 20 item *Temptation to Drink Scale*. This measure assesses how tempted an individual is to engage in a variety of health behaviors such as substance use. Confidence to avoid drinking will be measured using the 20 item *Abstinence Self-efficacy Scale*. This scale assesses an individual's confidence to abstain from drinking alcohol in various situations. Both scales assess temptation to drink or confidence to avoid drinking within these contexts: negative affect, social/positive, physical, and other concerns, and cravings/urges which may precipitate drinking [78, 79].

#### Readiness to change

*The Readiness to Change Questionnaire (Treatment Version; RCQ [TV])* assesses a patient’s level of readiness to change their alcohol use (e.g., reduce, quit) with respect to the precontemplation, contemplation, and action stages of change [80]. The RCQ (TV) includes 12 Likert-type items (3 per stage) ranging from −2 (*Strongly disagree*) to +2 (*Strongly agree*). A score is computed per subscale/stage, and the participant is assigned to the one with the highest score (in case where two or more scores are the same, participants are assigned to the stage that is furthest along the staging continuum [i.e., closer to action]).

#### Acculturation

Acculturation will be measured with the *Multidimensional Acculturation Scale II* (MAS II) [81]. The MAS II includes 22 items (from 0 [*does not apply to me*] to 5 [*very much/very well*]) assessing 4 factors: English proficiency, Spanish proficiency, identification with Mexican cultural identity, and identification with American cultural identity. MAS II factors have been found reliable (α = .78-.93).

#### Acculturative stress

Acculturative stress will be measured with the *Multidimensional Acculturative Stress Inventory (MASI),* which lists situations that Hispanics may have experienced within past 3 months [82]. The MASI includes 36 items ranging from 1 (*never*) to 5 (*daily or almost daily*). Identified factors are: Spanish competency pressures, English competency pressures, pressure to acculturate, and pressure against acculturation. Subscales (αs = .77 to .93), and the overall scale have demonstrated adequate reliability levels (α = .90) [82].

#### Therapeutic alliance

*The Helping Alliance Questionnaire (HAQ-II)* is part of the Penn Helping Alliance Scales [83, 84]. This self-report scale assesses experiences in therapy from both the patient and therapist's perspective. Thus, there is a patient version, and a therapist version. The HAQ-II includes 11 Likert-type items from 1 (*completely disagree*) to 4 (*completely agree*).

### Approach to analyses

Analyses investigating group differences in alcohol problems, and treatment utilization will use random coefficient models [85, 86]. Longitudinal models will use the following sequence of steps recommended by Singer and Willett [86]: 1) examine empirical growth plots, 2) fit an unconditional means model, 3) fit an unconditional linear growth model, 4) fit an unconditional non-linear model, 5) determine the best model of longitudinal change by comparing models in the previous two steps using the Akaike information criterion (AIC), 6) select the most appropriate error covariance structure using AIC, and 7) add level-2 predictors (e.g., intervention group).

Potential moderators will be examined by constructing interaction terms between treatment, and a priori moderator variables (e.g., acculturative stress and familism) to examine the possibility that the relation between a putative moderator, and outcome differ across treatments [87]. Mediation analysis (per recommendations by MacKinnon [2008]) will be conducted using a growth-curve framework implemented in an SEM [88]. Models will be constructed by first fitting growth models for mediators, and outcomes, and then fitting mediational growth models. Latent growth models will be comprised of at least two latent factors; one factor will represent the initial status, and one or more factors will represent the growth rate of a variable. The growth factor of the mediator will be regressed on the initial status of the mediator, the outcome, and the intervention group. A significant intervention effect establishes a relation between the intervention group, and the mediator, controlling for baseline levels of the mediator and outcome. Next, the growth factor will be regressed on the initial status of the mediator, the outcome, the slope of the mediator, and the intervention group. A significant effect of the mediator growth factor establishes a relation between change in the mediator, and change in the outcome, controlling for baseline levels of mediators and outcome.

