### Design and procedure

In this comparative effectiveness study, we will recruit 600 English- or Spanish-speaking heavy-drinking men of Mexican origin who are admitted to the hospital for medical treatment of an alcohol-related injury or heavy drinking. Participants will be randomized to receive a CA-BMI or NA-BMI. The primary outcomes of interest are alcohol use, alcohol problems, help-seeking, and treatment utilization. Follow-up assessments will be completed at 3, 6, and 12 months post-treatment. See Fig. 1.

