#### Randomization procedures

After obtaining informed consent, patients will complete the baseline assessment (described below). Subsequently, participants will be randomized to the CA-BMI or NA-BMI. Study staff will be blind to treatment assignment during the baseline assessment, and staff responsible for the assessment will not provide the intervention (vice versa). We will use an adaptive randomization procedure that minimizes imbalances in covariates [58] using a SAS macro [59]. This procedure ensures adequate distribution of key characteristics (i.e., acculturation, nativity, language of assessment) which have been found to influence outcomes [21].

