### Power analysis

Power for the hypothesized intervention effects was estimated using Monte Carlo studies. For longitudinal mixed models, a simulation was conducted (per example by Gelman and Hill) [89] using the *R* software, and power for mediation models was estimated using simulations in the *Mplus* software [90]. Culturally adapted interventions for other mental health problems have produced effect sizes of .45 [91]. The proposed effect size is informed by our previous study, which produced effect sizes between .25 and .32 with an average effect size of .28 [20, 92]. For this study, we estimated effect sizes equivalent to *d* = .28 for continuous outcomes and *h* = .28 for binary outcomes (nearly a 50 % increase in treatment utilization), using effect sizes for mixed models that are equivalent to these classical effect sizes [93].

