Power estimates were derived as the proportion of significant effects (two-tailed α = .05) across like simulations [94]. We simulated 10,000 data sets of 400 observations under the assumption that missing data will be ameliorated with the strategies described in the missing data section, and all participants will contribute data to the analysis. Intraclass correlation was simulated at .65 based on the intraclass correlations observed in our prior study. Power was .81 for continuous outcomes, and .83 for binary outcomes. A power analysis for a moderation effect by simulating a three-way interaction between treatment, time, and a moderator (e.g., familism) was conducted. Per Kraemer and colleagues’ recommendations, the interaction was examined using plots, confidence intervals, and *p* values [95]. We investigated the power for a hypothesized contrast at high, and low levels of a moderator (e.g., low v. high acculturative stress in participants in CA-BMI) through a simple slope contrast at 1 SD ± the moderator mean for participants [96]. Power for an effect size equivalent to *d* = .29 was .78 for a continuous outcome, and power for an effect size equivalent to *h* = .27 was .82 for a binary outcome. Power analysis for the proposed mediation model was conducted using a Monte Carlo simulation [90]. Using standardized regression coefficients, we conducted a simulation for 10,000 data sets in which the path from the intervention to the mediator was .12 (equivalent to *d* = .22), and the path from the mediator to the outcome was .30 for standardized variables, reflecting the stronger relation that we anticipate between the mediators and outcomes. The Monte Carlo simulation indicated that power for the indirect effect was .77. Thus, accounting for a potential 20 % participant attrition, the proposed sample size should provide sufficient power for all planned analyses.

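### Step 7 of the growth model leaves open how group relates to baseline; stating one shared pre-randomization baseline mean would make the arm contrast more precise at no cost

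*Protocol article*

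**What the plan says.** Under Approach to analyses, the comparisons of the arms on alcohol problems and treatment utilization "will use random coefficient models". The models are built in seven steps. The first six settle the shape of change and the error covariance without reference to arm. Arm enters only at the seventh, where the analyst is to "add level-2 predictors (e.g., intervention group". The text does not say whether group predicts initial status, rate of change or both, and it states no common baseline mean and no baseline covariate for this comparison.

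The mediation paragraph of the same section does mention baseline: "A significant intervention effect establishes a relation between the intervention group, and the mediator, controlling for baseline levels of the mediator and outcome".

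Three other sections bear on the point:
- Randomization procedures: "After obtaining informed consent, patients will complete the baseline assessment (described below). Subsequently, participants will be randomized to the CA-BMI or NA-BMI".
- Design and procedure: "Follow-up assessments will be completed at 3, 6, and 12 months post-treatment". With baseline this makes four waves.
- Power analysis: "Intraclass correlation was simulated at .65 based on the intraclass correlations observed in our prior study". It also says "we estimated effect sizes equivalent to *d* = .28 for continuous outcomes and *h* = .28 for binary outcomes", tests at "two-tailed α = .05", and reports power of .81 (continuous) and .83 (binary) for simulated data sets of 400.

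**The concern.** Baseline is completed before anyone is assigned, so the true arm difference at time 0 is zero. A growth model in which group predicts both initial status and slope estimates that difference anyway. The arm effect then becomes a contrast of change from each arm's own fitted baseline. A chance baseline difference feeds into it: the arm that happens to start higher tends to appear to improve more. Fixing the time-0 difference at its known value of zero removes part of that noise.

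What is at stake is precision on the primary outcomes. The simulated power of .81 leaves little to spare, and this gain would need no extra patients.

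**Working it through.** **Inputs from the protocol article.** Waves at 0, 3, 6 and 12 months; intraclass correlation .65; d = .28; two-sided alpha .05; 400 simulated, taken as 200 men per arm (an assumption, since the text says observations).

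**Further assumptions.** Continuous outcome, complete data, baseline variance 1 split into .65 between persons and .35 residual, a linear curve, and the effect of .28 reached at 12 months. Random-slope variance s (12-month units) and intercept-slope correlation r are not in the article, so ranges are shown.

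**1. The plan's own figure.** A plain two-sample comparison gives .28/√(2/200) = 2.80, and Φ(2.80 − 1.96) = Φ(.84) = .80, against the stated .81. This calculation uses neither the intraclass correlation nor baseline, so the match does not show which longitudinal model was simulated.

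**2. Time design.** With t = 0, .25, .5, 1: Σt = 1.75, mean .4375, Σt² = 1.3125, Sxx = 1.3125 − 1.75²/4 = .5469.

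**3. Per-person intercept b0 and slope b1.**
- Var(b0) = .65 + .35 × 1.3125/(4 × .5469) = .65 + .21 = .86
- Var(b1) = s + .35/.5469 = s + .64
- Cov(b0, b1) = r√(.65s) − .35 × .4375/.5469 = r√(.65s) − .28

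The difference between two arm means has 2/200 = .01 times the per-person variance.

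**4. Free against shared baseline.** With a free baseline, the slope contrast has variance .01 × Var(b1). With a shared baseline, the intercept difference is known to be zero, which leaves the conditional variance. The ratio (shared/free) is

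1 − Cov(b0, b1)² / [Var(b0) × Var(b1)],

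which cannot exceed 1.

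With no random slope the ratio is 1 − .28²/(.86 × .64) = 1 − .0784/.5504 = .858. The standard error falls from √.0064 = .0800 to .0741. The same precision would need about 400 × .858 = 343 men; equivalently, 1/.858 = 1.17, as if 17% more men were enrolled.

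| s | r | ratio | variance cut |
|---|---|---|---|
| 0 | – | .858 | 14% |
| .1 | 0 | .877 | 12% |
| .33 | 0 | .906 | 9% |
| .5 | 0 | .920 | 8% |
| .33 | −.3 | .790 | 21% |
| .5 | −.4 | .737 | 26% |
| .5 | +.5 | 1.00 | about 0 |

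**5. Other contrasts, no random slope.**
- Change to 12 months: free 2(1 − .65) = .70, shared 1 − .65² = .5775, ratio .825.
- Mean of the three follow-ups minus baseline: free (1 + 2 × .65)/3 + 1 − 2 × .65 = .4667, shared .7667 − .65² = .3442, ratio .738.

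**6. Sensitivity to the intraclass correlation (linear contrast, no random slope).** The ratio is .78 at .50, .858 at .65 and .92 at .80. The loss shrinks as the correlation rises.

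**7. Power at d = .28, 200 per arm, no random slope.** Free: Φ(.28/.0800 − 1.96) = Φ(1.54) = .94. Shared: Φ(.28/.0741 − 1.96) = Φ(1.82) = .97.

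**The case against.** The strongest reply is that the article never says group is put on initial status. A reader might infer that the plan has chosen a free baseline over a shared one. The text does not support that: a group effect on rate of change alone also fits the quoted words, and that already is a shared baseline. A condensed article may also leave this detail to the full plan. Both points stand, so the most that can be said is that the step leaves the choice open and that one answer is better than the other.

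A reader might also infer that group shifts only the overall level, so that the pre-randomization visit dilutes the effect. The documents speak against it. The sequence selects a model of change before adding group, and Power analysis simulates a treatment-by-time-by-moderator term, which presupposes treatment by time.

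It is also tempting to say that baseline information is thrown away, and more so because the intraclass correlation is high. Both parts are wrong. A free-baseline growth model already uses the time-0 wave to remove between-person variation, and step 6 of the working shows that the loss falls as the correlation rises.

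Nor is the mediation model's control for baseline a contradiction. It serves a different question, relating change in the mediator to change in the outcome.

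Finally, a free-baseline model is unbiased under randomization and keeps its type I error. That is correct, and it limits the point to efficiency.

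**Conclusion.** The point holds as a free improvement. If group predicts both initial status and rate of change, the arm contrast is valid but has more variance than necessary. At the plan's intraclass correlation and with no random slope, the excess removed by a shared baseline is about 14% for the linear contrast. Under the assumed random slopes it is about 8% to 26% for zero or negative intercept-slope correlation, and close to nothing at +.5. It is never negative, given the same model otherwise. If group predicts rate of change only, the gain is already in hand and the wording merely confirms it.

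These figures are for continuous, complete data. Binary and count outcomes, and data with the attrition the plan expects, will give different percentages.

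A reader might want to restate the plan's power of .81 as a higher figure. The article does not allow that, because it does not say which model was simulated. With its intraclass correlation alone, power goes from .94 to .97. A slope variance of .33 would give √(.01 × .97) = .0985 and power Φ(.28/.0985 − 1.96) = .81 for the free version, rising to .85 (r = 0) or .89 (r = −.3) with a shared baseline. That variance was picked to match the stated figure and has no source in the article.

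**What to change.** In step 7 of Approach to analyses, state for all primary outcomes:
- baseline is the first outcome occasion;
- both arms share one baseline mean (one baseline log-odds for binary outcomes);
- intervention group enters only through its interaction with time since baseline, with no group term at time 0.

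For continuous outcomes, modelling the follow-ups with the baseline value as a covariate is an acceptable alternative. For binary outcomes the two are not interchangeable: conditioning on baseline targets a different odds ratio, because odds ratios are non-collapsible. One version should be chosen and named there.

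The cost is a line or two of model specification. No new data, visits or patients are needed, and the constraint is justified because randomization follows the baseline assessment.
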